### Hypotheses

The main objective of this trial is to determine the efficacy of the 12-week Selfapy course for patients with GAD compared to a wait-list control group. Additional outcome data will be collected at 6 weeks. However, our confirmatory hypotheses, which will evaluate a positive health care effect, will focus on the 12-week outcomes. The following 2 hypotheses refer to our primary outcomes:

GAD symptomatology (measured with the GAD-7 [27]) will significantly decrease with the use of the Selfapy course for GAD after 12 weeks compared to a wait-list control group.Perceived quality of life (measured with the WHO-5 [28]) will significantly increase after 12 weeks of the Selfapy course for GAD compared to a wait-list control group.

The following secondary outcomes will only be analyzed if the hypotheses for the primary outcomes are confirmed. They will also be tested using Bonferroni-Holm adjustment:

Difficulties in daily life (measured with the WSAS [30]) will significantly decrease after using the Selfapy course for GAD after 12 weeks compared to a wait-list control group.Using the Selfapy course for GAD will lead to significantly better recovery of working ability (measured with the iPCQ [32]) after 12 weeks compared to a wait-list control group.Health literacy (measured with the MHLS [34]) will significantly improve with the use of the Selfapy course for GAD after 12 weeks compared to a wait-list control group.The extent of therapy-related efforts and burdens of patients and their relatives (measured with the CSSRI [35]) will be significantly reduced after using the Selfapy course for GAD compared to a wait-list control group after 12 weeks.

Our exploratory hypotheses do not address the target symptoms and are therefore not adjusted for α accumulation:

Worry symptoms (measured with the PSWQ [36]) will significantly decrease with the use of the Selfapy course for GAD after 12 weeks compared to a wait-list control group.Self-rated anxiety symptoms (measured with the BAI [39]) will significantly decrease with the use of the Selfapy course for GAD after 12 weeks compared to a wait-list control group.Self-rated depressive symptoms (measured with the PHQ-9 [41]) will significantly decrease with the use of the Selfapy course for GAD after 12 weeks compared to a wait-list control group.The Selfapy course for GAD will not lead to any side effects compared to a wait-list control group after 12 weeks (measured with the NEQ [42]).

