### Measures

Table 1 provides an overview of survey instruments at each time point, and more detailed descriptions are also provided below.

**Table 1 table1:** Survey instruments at each time point.

Time point	Survey instrument
Pretreatment measurement (T1)	Video interview: Diagnostic Interview in Mental Disorders–Open Access (DIPS-OA). Primary outcomes (self-assessed via web-based questionnaire) Generalized anxiety disorder symptomatology (Generalized Anxiety Disorder–7; GAD-7) Quality of life (World Health Organization–Five Well-Being Test; WHO-5) Secondary outcomes (self-assessed via web-based questionnaire) Coping with difficulties in everyday life due to illness (Work and Social Adjustment Scale; WSAS) Work Capability (Institute for Medical Technology Assessment Productivity Cost Questionnaire; iPCQ) Health Literacy (Mental Health Literacy Scale; MHLS). Reduction of therapy-related expenses and burdens for patients and their relatives (Client Sociodemographic and Service Receipt Inventory; CSSRI) Secondary outcomes Demographic questionnaire Anxiety symptomatology (Beck Anxiety Inventory; BAI) Depressive symptoms (Patient Health Questionnaire–9; PHQ-9)
Intermediate measurement 6 weeks after T1 (T2)	Same as T1, except that there is no video interview Further surveys Negative effects (Negative Effects Questionnaire; NEQ) Short demographic questionnaire
Posttreatment measurement 12 weeks after T1 (T3)	Same as T2

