### Additional Outcomes

The Penn State Worry Questionnaire (PSWQ [36]) is used to assess worry as an accompanying syndrome of GAD; it consists of 16 items rated on a 5-point Likert scale. The PSWQ shows internal consistencies approximately in the range between α=.84 [37] and α=.86 [38] in GAD patients.

The Beck Anxiety Inventory (BAI [39]) is used to assess the severity of anxiety in adults and adolescents. It consists of 21 descriptive statements rated on a 4-point scale. The internal consistency of the BAI is α=.90 in clinical samples. The German version was validated by Margraf and Ehlers [40].

The Patient Health Questionnaire-9 (PHQ-9 [41]) is used to assess the presence and severity of depressive disorders. The PHQ-9 consists of 9 items rated on a 4-point Likert scale and has an internal consistency of α=.89.

To capture possible negative effects of the intervention, the Negative Effects Questionnaire (NEQ [42]) is used, which consists of 32 items rated on a 4-point Likert scale. The NEQ has an internal consistency of α=.95.

The adherence of the intervention group is recorded via the log files of the web-based platform Selfapy. The number of modules that have been worked on is recorded.

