### Power and Sample Size

The between-group effect size estimate is based on recent meta-analytic evidence for effect sizes in unguided web-based psychological interventions for anxiety disorders (Cohen *d*=0.45; see, for example, McCall et al [46]). Even though Selfapy is minimally guided, we chose this meta-analysis since the degree of guidance is not associated with the effect size [16,17]. This effect size will be used as the basis for sample size design. For the planned mixed model with 2 measurement time points with a general correlation structure [47], a directed hypothesis, a group allocation of 1:1, a power of 0.80, and an α level of .025 after Bonferroni-Holm correction, a total of 156 patients (n=78 per group) are needed. The number of cases was calculated using the R tool *longpower* [48]. For the secondary outcomes, this sample size yields a power of 1–β=.67.

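### The exploratory safety hypothesis claims no side effects without a margin or interval criterion, so the trial as described cannot demonstrate it

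*Protocol article*

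**What the plan says.** The Hypotheses section lists ten hypotheses: two primary, four secondary and four exploratory. Nine of them predict a significant change or difference in favour of the course. The tenth, on safety and measured with the NEQ, predicts that nothing will be found: "The Selfapy course for GAD will not lead to any side effects compared to a wait-list control group after 12 weeks". It belongs to the exploratory group, which is outside the multiplicity scheme: "Our exploratory hypotheses do not address the target symptoms and are therefore not adjusted for α accumulation".

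Under Additional Outcomes the instrument is introduced as follows: "To capture possible negative effects of the intervention, the Negative Effects Questionnaire (NEQ [42]) is used, which consists of 32 items", rated on a 4-point scale. Table 1 in the Measures section lists it from T2 onward: "Further surveys Negative effects (Negative Effects Questionnaire; NEQ").

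The Power and Sample Size section sizes the trial for efficacy only, from a meta-analytic effect for "unguided web-based psychological interventions for anxiety disorders (Cohen *d*=0.45"), with "a directed hypothesis, a group allocation of 1:1, a power of 0.80, and an α level of .025 after Bonferroni-Holm correction", giving 78 per group. It gives no power, standard deviation, event rate or acceptable difference for the NEQ. The Statistical Analyses section describes a mixed model for the primary and secondary outcomes. It also names t tests and chi-squared tests for baseline characteristics, response rates and service use. None of these methods is assigned to the NEQ.

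**The concern.** A hypothesis that an intervention has no side effects is the null hypothesis of an ordinary difference test. Failing to reject that null does not show it to be true. To support a claim of this kind, a plan needs either a stated margin with a test that excludes harm beyond it, or a rule based on the confidence interval. The article has neither. Because the other nine hypotheses are to be supported by significance, the easy counterpart for this one is to call it supported when the NEQ difference is not significant.

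At stake is what the trial may say about safety. A report could state that the course has no side effects when the data are also compatible with a small to moderate excess of negative effects. The smaller the number of analysed participants, the easier that statement would be to reach.

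**Working it through.** **Inputs from the article.** 78 per arm; planning effect d = 0.45; directed hypothesis; α = .025; power 0.80; 1:1 allocation (Power and Sample Size).

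**Assumptions.** The article gives no NEQ effect, SD, event rate or test level. I work in SD units, with a two-sided level of 0.05, complete data, and true excesses of 0.2, 0.3 and 0.45 SD. The last equals the article's efficacy planning effect and serves only as a reference point.

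**1. The article's own sample size.** Per arm, n = 2(1.960 + 0.842)² / 0.45² = 77.5, rounded up to 78, or 156 in total. This matches the stated figure, so a simple two-group comparison of means is a fair basis for the remaining steps.

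**2. Precision of the NEQ difference.** The standard error in SD units is √(2/78) = 0.160. The 95% CI half-width is 1.96 × 0.160 = 0.31 SD. An observed difference of exactly zero would therefore still be compatible with an excess of about 0.31 SD.

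**3. Chance of a non-significant result when harm is real.** The noncentrality is d × √(78/2) = 6.245d, and the chance of non-significance is about Φ(1.96 − 6.245d).

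| Assumed true excess | 6.245d | Chance of non-significance |
|---|---|---|
| 0.2 SD | 1.25 | 76% |
| 0.3 SD | 1.87 | 53% (54% with the t distribution) |
| 0.45 SD | 2.81 | 20% |

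With 62 per arm (an assumed loss of about 20%), the same formula gives 80%, 61% and 29%.

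**4. What a test to exclude harm could show.** With one-sided 0.025, 80% power and a true difference of zero, the smallest margin that 78 per arm can exclude is (1.960 + 0.842) × √(2/78) = 0.45 SD. A margin of 0.3 SD would need 2(2.802)²/0.3², or 175 per arm. A margin of 0.2 SD would need 393 per arm. These margins are illustrations, as the article states none.

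**5. Zero events.** If none of 78 intervention participants reported a given negative effect, the upper limit for its rate would be 1 − 0.025^(1/78) = 4.6% (two-sided 95%), or 1 − 0.05^(1/78) = 3.8% (one-sided 95%).

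**The case against.** The strongest reply is that the article never says how the NEQ will be tested, nor that a non-significant result will be taken as proof of safety. The hypothesis is labelled exploratory, its sentence does not mention significance, and a statistical analysis plan that is not shown may contain interval reporting. This stands in part. The use of non-significance as support is an inference from the wording and from the methods described, not a stated rule. But an absolute claim of no side effects cannot be demonstrated by this sample under any analysis the article describes. That fault is in the hypothesis as written and is not a detail left to another document.

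It is also fair to say that the sample is not uninformative. With complete data, power is about 80% for an excess of 0.45 SD, so a moderate harm would probably be seen. Safety handling during the trial does not depend on this hypothesis either: the Study Design section provides for monitoring by a psychologist, and suicidality is asked about at every time point.

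Three stronger readings are tempting, but the documents do not support them:

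- **The model cannot be applied.** With no T1 value, a baseline-to-T3 group-by-time model would not fit the NEQ. The article never assigns that model to the NEQ, and first asking about negative effects after treatment has begun is not an error.
- **The wait-list comparison hides harm.** If wait-list participants cannot report effects of a treatment they have not received, their scores would tend to be lower. That would widen the gap between arms, not conceal it. They may also use other treatment and report on that.
- **The suicidality rule biases the result towards safety.** Under Ethical Considerations, the exclusion of later data after suicidality is endorsed applies to all participants. The direction of any effect on the NEQ contrast is not shown.

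**Conclusion.** The point holds in a limited form. The exploratory safety hypothesis is a no-effect claim without a margin or interval criterion, the described methods are difference methods, and the trial therefore cannot demonstrate it. At 78 per arm an excess of 0.2 to 0.3 SD would more often than not give a non-significant result (76% and 54%), and one of 0.45 SD would do so about one time in five. These figures rest on assumed effect sizes, complete data and a two-sided 0.05 level. Dropout would make them worse.

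Severity is modest. The hypothesis lies outside the confirmatory hierarchy, so no primary or secondary conclusion, error rate or sample size depends on it. What changes is the safety statement that the trial can properly make.

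**What to change.** Replace the hypothesis with an estimation aim. Report NEQ results by arm at T2 and T3, and give the between-arm difference at T3 with a 95% confidence interval. State that a non-significant difference will not be read as absence of side effects. Deterioration on the GAD-7 and PHQ-9, which Table 1 lists for both arms from T1, may be added descriptively. Shares of effects attributed to treatment should not be promised, because the article does not document that attribution is recorded.

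The cost is a change of wording and a small table from data already collected. The claim of no side effects is given up. If the sponsor wishes to keep a claim of that kind, a justified margin is needed, and at 78 per arm only margins of about 0.45 SD or larger could be excluded with 80% power.

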### Intervention

Selfapy is a program for the treatment of GAD [43]. The program uses evidence-based methods and exercises based on CBT and elements of mindfulness-based therapy (see, eg, Hoyer et al [44] and Volz and Stieglitz [45]). The web-based course consists of a core course, which includes mandatory and optional exercise content, and a subsequent set of modular specialization areas that are individually selectable (Table 2). The program can be used via desktop browsers and mobile devices. The web-based course is divided into different lessons, each covering a specific topic, such as exposure, mindfulness, or problem-solving training, and consists of informative texts, videos, audio, and interactive exercises. Table 2 provides an overview of the core course with examples and possible in-depth areas and gives a brief overview of their content.

**Table 2 table2:** Overview of modules with example content of the generalized anxiety disorder program.

Module		Content
Your start		In the first module, users can describe their problems and set personal goals.
First findings		This module focuses on psychoeducation. Users learn to recognize and understand the background of their problems. In addition, users begin keeping a worry log to identify triggers and patterns regarding their worries and fears.
The mental level		This module deals with the thoughts behind the users’ anxiety disorder. With the help of various exercises, users learn to question their worries and replace them with more realistic thoughts.
The physical level		In this module, users learn about the fear response and the physical symptoms of generalized anxiety disorder.
The behavioral level		In this module, users learn about how avoidance and reassurance contribute to maintaining their anxiety disorder and how the 3 levels of anxiety interact.
The first exposure		In this module, users are introduced to exposure-based methods. They learn how exposure works and why it is helpful in the treatment of anxiety disorders. Users will also receive information on how to perform an in sensu exposure and consider when to do so.
The second exposure		This lesson is dedicated to in vivo exposure. Users are informed about what it looks like and what to consider when performing it.
**Optional areas of specialization**		
	Self-efficacy	In this module, users learn about self-efficacy. Through various exercises, they are trained in self-efficacy so as to believe more in themselves and their abilities.
	Mindfulness	A mindful approach to life can have a supportive effect to better deal with one’s problems. With the help of formal and informal mindfulness exercises, users learn how to integrate a mindful approach to themselves into everyday life.
	Social environment	This module deals with the impact of the social environment on one’s own life. Through social networks and communication exercises, users can optimize their social support and strengthen their social skills.
	Problem solving training	This module provides training in problem-solving skills. Users learn to perceive a concrete problem, grasp reaction possibilities, and implement an action to change the situation.
	Your anti-anxiety package	In the final module, users take stock of the completed course. They summarize which content was particularly helpful and where they can still improve their anxiety disorder. At the end of the program, the user gains an antianxiety package to use when problems arise again or a relapse has already set in.

### Randomization and Blinding

Subjects meeting the inclusion criteria will be randomly assigned to 1 of 2 groups and will receive either (1) immediate access to the minimally-guided Selfapy GAD course (the intervention group) or (2) access to the Selfapy GAD course after a waiting period of 12 weeks (the control group).

Randomization takes place after the participant has finished the entry questionnaire, which is conducted by a member of the psychology department who is not involved in the project, using a computer-assisted procedure. Random assignment is done only if participants fulfill the inclusion criteria for the study. Until this time, which group the person will be assigned to if included is unknown (allocation sequence concealment). Participants will be assigned to 1 of the 2 groups in a nonstratified 1:1 ratio. Subjects will be informed of the outcome of the random assignment via email. Participants are told that the waiting time will randomly vary between 0 and 12 weeks. Thus, patients in the control group will not know that the sample is divided into 2 groups. One group will start the intervention immediately while the other group will wait 12 weeks before receiving access to the therapy. The diagnostic interviewers will be blind to the group membership of the participants. After completing data collection, statistical analysis of the outcomes will also be performed in a blinded manner.

### Power and Sample Size

The between-group effect size estimate is based on recent meta-analytic evidence for effect sizes in unguided web-based psychological interventions for anxiety disorders (Cohen *d*=0.45; see, for example, McCall et al [46]). Even though Selfapy is minimally guided, we chose this meta-analysis since the degree of guidance is not associated with the effect size [16,17]. This effect size will be used as the basis for sample size design. For the planned mixed model with 2 measurement time points with a general correlation structure [47], a directed hypothesis, a group allocation of 1:1, a power of 0.80, and an α level of .025 after Bonferroni-Holm correction, a total of 156 patients (n=78 per group) are needed. The number of cases was calculated using the R tool *longpower* [48]. For the secondary outcomes, this sample size yields a power of 1–β=.67.

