While most of the literature focuses on guided forms of iCBT with therapeutic support, minimally guided, self-directed iCBT programs also show large effect sizes in the treatment of GAD (eg, Cohen *d*=2.43 [21]). Dear et al [22] found no significant differences between guided and unguided iCBT in terms of symptom reduction, completion rates, and satisfaction in the treatment of GAD. Moreover, first evidence suggests that characteristics of the guidance, such as the frequency of supportive monitoring [23], type of reminder (eg, phone, email), and the experience or training of the support person [24], do not have a significant influence on GAD symptom reduction. Nevertheless, it is important to take steps to promote adherence and minimize the typically high dropout rates of web-based, particularly self-directed, interventions [25] (eg, motivational content).

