### Statistical Analyses

For the psychometric outcome analyses, all patients who were randomly assigned to the 2 conditions and completed the initial survey (T1) will be included in an intention-to-treat (ITT) analysis. All available data will be used for this purpose. Missing values in the data will be replaced by multiple imputations (multivariate imputation by chained equations with n=5 imputations) based on the control arm, using the variables “age” and “gender” as predictors in addition to the measurement-repeated stress indicators. In addition, last-observation-carried-forward, baseline-observation-carried- forward, reference-based-multiple imputation (jump-to-reference approach [49]), and completer sensitivity analyses will be performed.

The confirmatory analysis of the primary outcomes consists of calculating a mixed model with 2 measurement time points and a general correlation structure [47]. A random effect for the subjects is calculated (random intercept) and 3 fixed effects (group assignment, time, and the interaction of the 2 predictors). The 2 measurement time points are nested within subjects. The primary outcomes will be evaluated using a Bonferroni-Holm correction for α error inflation. Secondary confirmatory outcomes will only be analyzed if the results of the primary analysis confirm the hypotheses, and the same mixed model with a random intercept for the subject will be applied. Again, a Bonferroni-Holm correction will be used.

Independent 2-tailed *t* tests and chi-squared tests will be used to estimate differences between groups in pretreatment sample characteristics. In addition to the ITT sample, a “per-protocol” sample sensitivity analysis is defined for exploratory analyses, including all patients in the intervention group who completed at least 4 of the modules.

There are different approaches to calculating effect sizes for mixed modeling data in the literature [50]. Hedges [50] and Westfall et al [51] propose an effect size based on the Cohen *d*, which is also used for power analysis [47]:

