## Discussion

This study tests the efficacy of a minimally guided web-based intervention (Selfapy) for the treatment of GAD in routine clinical care. The study has several strengths. First, the study was designed to strike a balance between a high degree of internal validity (eg, randomization, a standardized diagnostic procedure), allowing us to attribute observed group differences to the intervention with sufficient certainty and a high external validity (eg, allowing participants to use additional health care services) to evaluate the effects in an ecologically valid context. In particular, we did not prepare artificial measures to increase adherence to gain a representative impression of routine care patient adherence. Second, to the best of our knowledge, this study is one of the most highly powered studies on iCBT for GAD [13]. Third, we will investigate outcomes beyond symptom reduction, such as functioning and health care use. Limitations of this study include the lack of an active control group instead of a wait-list control group, even though this design allows only limited conclusions regarding the specificity of the effects found. We chose this design in an attempt to assess the incremental effect of Selfapy for GAD patients compared to the current situation in the German health care system. Patients who want to undergo outpatient psychotherapy in Germany have to wait for an average of 20 weeks to start treatment [19]. One of the main advantages of an internet intervention like the one investigated in this study is its availability. If implemented in routine clinical care, patients can make use of these interventions without delay and can expect results comparable to traditional face-to-face therapy [14]. One could argue that the waiting period in the control group (12 weeks) is too short, given the average waiting time in the health care system of 20 weeks. Still, we decided to restrict the waiting time in the control group to 12 weeks for several reasons. First, for ethical reasons, we wanted to limit the waiting time as much as possible. Withholding a likely helpful intervention should only be done as long as necessary. Again, we want to highlight that patients in the control group, as well as those in the intervention group, were allowed to seek additional treatment and help if they thought it necessary. No patients were asked to refrain from any other mental health services. Second, 12 weeks is the time the intervention takes when completed on the recommended schedule. Therefore, fixing the control group to the same measurement schedule as the intervention allows us to evaluate the effects of having access to Selfapy for GAD compared to not having access to this intervention. Another limitation lies in the use of deception in telling the patients that the intervention will start some time between 0 and 12 weeks later. This is done to attenuate dissatisfaction with being in the control group. However, patients in the control group may still feel dissatisfied and unlucky when they have to wait what they think is the maximum amount of time for the intervention. Also, we do not assess the frequency of personality disorders, which may be reasonable because GAD is associated with higher rates of personality disorders [53]. Further limitations include the lack of follow-up measurement, the lack of a power calculation for the secondary outcomes, and the lack of a mindfulness measure despite the intervention including a mindfulness-based approach.

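### The stated 80% power at 156 patients holds only with complete T3 data, yet the plan provides for missing outcomes and imputes them from the control arm

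*Protocol article*

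**What the plan says.** The Power and Sample Size section takes its effect size from meta-analytic evidence on "unguided web-based psychological interventions for anxiety disorders (Cohen *d*=0.45"). It plans for "a directed hypothesis, a group allocation of 1:1, a power of 0.80" and "an α level of .025 after Bonferroni-Holm correction", and concludes that "a total of 156 patients (n=78 per group) are needed". Attrition and missing data are not among the inputs listed. The Abstract gives the same 156 (78 and 78) as the recruitment figure.

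The Statistical Analyses section includes every randomised patient with a completed T1 survey. It fills missing values by "multivariate imputation by chained equations with n=5 imputations) based on the control arm", with age, gender and the repeated measures as predictors. It adds four sensitivity analyses for missing data: last observation carried forward, baseline observation carried forward, jump-to-reference imputation and completers. Under Ethical Considerations, assessments after a participant endorses suicidality are not used, which is a further possible source of missing T3.

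**The concern.** The number needed and the number recruited are the same, so every randomised patient must supply a T3 score for the stated power to hold at the planning inputs. The analysis section does not expect that. Two things then work against the 0.80: fewer patients contribute T3 information, and imputing intervention-arm gaps from control-arm behaviour reduces the expected group difference, while the calculation uses the undiluted 0.45.

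At stake is how a non-significant primary result is read. In a trial described as having "a power of 0.80", it would count as fairly strong evidence against the programme. The secondary outcomes are analysed only if the primary hypotheses are confirmed, so low power on the primaries also closes that family.

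**Working it through.** **Inputs from Power and Sample Size.** d = 0.45 (SD = 1), one-sided α = .025, power 0.80, 1:1 allocation, 78 per arm.

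**Inputs assumed because the article gives none.** Missing T3 of 10, 20 or 30%, equal in both arms; T1–T3 correlation ρ = 0.5.

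**1. Reproducing the plan's figure.**
- n per arm = 2(z₀.₉₇₅ + z₀.₈₀)²/d² = 2(1.960 + 0.842)²/0.45² = 77.5, rounded up to 78, or 156 in total.
- Power at 78 = Φ(0.45·√(78/2) − 1.960) = Φ(2.810 − 1.960) = 0.802.
- In a change-score or time-by-group model the SD of the change is √(2(1−ρ)). This equals 1 at ρ = 0.5 and again gives 78.

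The arithmetic is right, and it uses all 156 patients with no loss.

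**2. Missing T3, full effect kept.** With a proportion q missing, power = Φ(0.45·√(78(1−q)/2) − 1.960). At q = 0.20: 78 × 0.80 = 62.4 and 0.45·√31.2 = 2.514, so Φ(0.554) = 0.71.

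**3. Missing T3, effect diluted.** If intervention-arm patients without T3 are imputed to behave like controls, the expected difference is about (1−q)·0.45.
- With the complete-data standard error, power = Φ((1−q)·0.45·√(78/2) − 1.960).
- With the standard error also inflated for lost information, power = Φ((1−q)·0.45·√(78(1−q)/2) − 1.960). At q = 0.20: 0.36·√31.2 = 2.011, so Φ(0.051) = 0.52.

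| Missing T3 in each arm | Full effect kept | Diluted, complete-data SE | Diluted, SE inflated |
|---|---|---|---|
| 0% | 0.80 | 0.80 | 0.80 |
| 10% | 0.76 | 0.72 | 0.67 |
| 20% | 0.71 | 0.61 | 0.52 |
| 30% | 0.65 | 0.50 | 0.38 |

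A simulation of control-based multiple imputation (5 imputations, Rubin's rules, ρ = 0.5, half of those without T3 also lacking T2) gave 0.54 at 20% and 0.40 at 30%, close to the last column.

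**4. Sensitivity to the assumed correlation, at 20% missing T3.**

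| ρ | Full effect kept | Diluted, SE inflated |
|---|---|---|
| 0.5 | 0.71 | 0.52 |
| 0.6 | 0.80 | 0.61 |
| 0.7 | 0.90 | 0.74 |

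With T2 data used as in the simulation above, the figure for control-based imputation at ρ = 0.7 and 20% missing was 0.79. A correlation below 0.5 works the other way: at 0.4 the complete-data requirement is already 94 per arm.

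**5. Holm's second step.** If both primary outcomes have d = 0.45, a single outcome can also be declared at .05 once the other has passed .025. With complete data this raises its power to about 0.85. With 20% missing T3 it is about 0.77 (full effect) or 0.58 (diluted, SE inflated).

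**The case against.** **The figure is arithmetically correct, and the article is condensed.** Both are true. But the section publishes a full derivation with a definite conclusion, and the analysis described alongside it does not meet the condition that the conclusion depends on. The point concerns a stated claim, not a missing detail.

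**Dropout is not the same as missing T3.** The Background refers to the need to "minimize the typically high dropout rates of web-based, particularly self-directed, interventions", and Study Design counts as a dropout someone who finishes no module over 4 weeks. Such a person can still complete the T3 questionnaire and stays in the analysis. This stands: the article forecasts no rate of missing outcomes. It also describes monitoring by a psychologist and an allowance paid on completing the study, both of which may support T3 completion. The 10 to 30% range is therefore an assumption.

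**The dilution depends on how the imputation is read.** Jump-to-reference is listed separately as a sensitivity analysis, so the primary imputation may be something milder, and T2 scores could carry part of an early benefit forward. The article also does not say whether 0.45 already reflects attrition in the source trials; if it does, dilution is partly counted twice. These points bear on the two diluted columns. They do not remove the loss in the full-effect column at ρ = 0.5.

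**Stronger readings that a reader might infer, and that the documents do not support:**
- *That true power is near 50%.* This is one part of a wide grid and depends on the missing rate, the correlation and the reading of the imputation.
- *That the one-sided test is a hidden weakness.* It is declared ("a directed hypothesis, a group allocation of 1:1, a power of 0.80"), and the primary hypotheses are directional. The 2-tailed tests in Statistical Analyses concern baseline characteristics, response rates and service use, not the primary model. Power of 0.715 at 78 per arm, with 94 per arm needed, applies only if the primary tests are run two-sided at .025, which the article does not say.
- *That the Discussion's statement that "this study is one of the most highly powered studies on iCBT for GAD" is false.* It is hedged and comparative, other trials also lose patients, and its source is not available here.

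**Participation has ended.** So nothing in the design can change, and confidence intervals will show the precision achieved. That limits the remedy to wording but does not make the unconditional 80% correct.

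**Conclusion.** The statement is wrong as written, in a limited sense: 156 patients give 80% power only if every patient has a T3 score. At the correlation that reproduces the plan's own figure, any missing T3 takes power below 0.80: to between 0.76 and 0.67 at 10%, between 0.71 and 0.52 at 20%, and between 0.65 and 0.38 at 30%. The upper value keeps the full effect; the lower one takes control-arm imputation literally and counts the lost information.

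These sizes rest on an assumed missing rate, equal loss in both arms, ρ = 0.5 and first-step testing at one-sided .025. A correlation of 0.6 or more, T2 data in the imputation, or Holm's second step would recover part or, in the milder cases, all of the loss. The plan does not claim any of these as a reserve. Type I error is not affected.

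**What to change.** Add no patients. In Power and Sample Size, state that 80% refers to complete T3 data and a one-sided .025 test. Then give power at the planning effect of 0.45 for a stated range of missing T3 (for example 10, 20 and 30%) under the imputation actually used, naming the T1–T3 correlation assumed. As the article's text is fixed, the same statement can go into the results report.

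Repeating in Statistical Analyses that the primary tests are one-sided would be a minor clarification, not the correction of an error.

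The cost is a few sentences and a small table. No data, test or error rate changes, and the stated power becomes conditional and less favourable.
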